##### CPR Development

SHAP will be used to ‘translate’ model insights into CPRs. Mean—and not mean *absolute*—SHAP values will be used in order to preserve information on the directionality of feature importance. The decile rank of each of the eight mean SHAP values from each model will be calculated and a dot plot will be provided to visualise each feature’s mean SHAP value relative to others. (We speak of eight mean SHAP values because we have eight predictor variables corresponding to the features of CHA_2_DS_2_-VASc, namely five comorbid items, sex, and *two* age categories [65–74 years and ≥75 years]). The 25th, 50th, and 75th percentiles of the eight mean SHAP values will be computed. We will subsequently rank the features from most to least important and sort them into three tiers: (1) the lower tier grouping features with mean SHAP values below the 25th percentile, (2) the middle tier grouping features with mean SHAP values between the 25th and 75th percentiles, and (3) the upper tier grouping features with mean SHAP values above the 75th percentile. Features belonging to the lower, middle, and upper tiers will be assigned one, two, and three points, respectively. The purpose of a larger middle tier is to avoid over- or understating the importance of features by promoting stability over frequent changes with minor shifts in model parameters. In the rather unlikely event that one or more features will have negative mean SHAP values and local SHAP value distributions that are consistently left of zero on the beeswarm plots, zero points will be assigned, because their inclusion would degrade 90-day recurrence predictive performance. Ties at quantile cut-points will be resolved conservatively by assigning them to the higher category (e.g., features tied at the 75th percentile will enter the upper tier). The resulting CPRs will be summarised in tabular form and given an acronym in likeness to CHA_2_DS_2_-VASc.

If the dot plot suggests that the distribution of mean SHAP values is very skewed or concentrated, the above-defined tiers will probably inadequately capture features of lower, intermediate, and higher importance. In this eventuality, we will tailor tier boundaries using quantile-based binning. After adapting the tier setup to the observed clusters, we will define lower, middle, and upper tiers whose features will be assigned one, two, and three points, respectively.

Each of the CPRs will subsequently be augmented by integrating interaction effects. This purports to better accommodate for the fact that a given feature may be more impactful in the presence of one of its counterparts. Mean (and not mean *absolute*) SHAP interaction values will be used in order to distinguish between synergistic and redundant interactions. The decile rank of each of the twenty-eight mean SHAP interaction values from each model will be calculated. A dot plot will be provided to visualise each feature-pair’s mean SHAP interaction value relative to other pairs. (We speak of twenty-eight mean SHAP interaction values because there are eight features, and (*i*, *j*)- and (*j*, *i*)-values capture the same interaction effect, while (*k*, *k*)-values capture main effects and were the object of the above paragraph). Dealing with a large number of feature-pairs, we will use stringent percentiles in selecting interaction effects for inclusion. The 90th percentile of the sample of twenty-eight mean SHAP interaction values will be computed. Feature-pairs with mean SHAP values above this threshold will be selected as the most important synergisms. Feature-pair selection will also incorporate domain knowledge, as some feature-pairs have well-established synergisms that may merit inclusion even if they fall somewhat short of the 90th percentile cutoff. Examples include CHF and age [121], hypertension and age [122], and hypertension and DM [123]. Selected feature-pairs will be integrated into the CPRs as accompanying rules: ‘if both feature *i* and *j* of the pair are present in the patient, add one additional point to the patient’s total score’. To mitigate overfitting, we will cap the number of points that can be added to accommodate synergisms to three. We will further cap the number of interaction pairs retained at a maximum of three. The augmented CPRs will be summarised in tabular form and their acronyms labelled with an asterisk (e.g., CHA_2_DS_2_-VASc*). A worked example of the CPR development process here described can be found in Appendix S6 in Supplementary Materials file S3.

Both non-augmented and augmented CPRs will undergo evaluation. See “CPR Evaluation”.

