##### Global Interpretation

To summarise the average impact of each feature on our models’ outputs across the test set, we will calculate mean absolute SHAP values. The absolute mean will also be taken across SHAP interaction values. SHAP summary plots will be provided: bar plots to depict mean absolute SHAP values, and beeswarm plots to depict the distribution of local SHAP values in order to intuitively understand variability. We will also provide 8 × 8 beeswarm plots which depict interaction effects in the off-diagonal entries of the feature grid, 28 of which are unique owing to the symmetry of SHAP interaction values.

SAGE values will be reported with regard to the AUC and graphically represented using bar plots. Unlike SHAP, the SAGE algorithm readily provides the standard error of each feature’s importance. These will be utilised to gauge the stability of the importance estimates and facilitate their comparison.

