Primary: Does the acute context of AFAIS, and the importance of the index event, call for a CPR bespoke to early secondary prevention? In other words, are the main effects of the constituent features of CHA_2_DS_2_-VASc different post-stroke? Besides main effects, are there synergistic or other non-linear interaction effects between stroke history and the constituent features of CHA_2_DS_2_-VASc that can further improve prediction of 90-day AFAIS recurrence? Secondary: How do CPRs trained to capture 90-day AFAIS recurrence perform with regard to secondary outcomes (7-day recurrence, 7- and 90-day HT, 90-day decline in functional status, and 90-day all-cause mortality)? Exploratory: How do CPRs trained to capture 90-day AFAIS recurrence perform with regard to recurrence among non-AF AIS patients?	Primary: LR and XGBoost can capture the main effects of the constituent features of CHA_2_DS_2_-VASc in the context of secondary prevention. XGBoost is also equipped to capture complex functional relationships between the features. The outputs of these models can be employed to construct CPRs that outperform CHA_2_DS_2_-VASc for predicting 90-day recurrence in AFAIS patients. Specifically, fair (AUC < 0.8) to good (< 0.9) discrimination can be achieved for this high-risk group, alongside improved calibration and clinical utility relative to CHA_2_DS_2_-VASc. Secondary: The resulting CPRs also outperform CHA_2_DS_2_-VASc for predicting secondary outcomes.	LR and XGBoost models: Discrimination assessed using AUC and calibration curves. Calibration assessed using calibration curves, slopes, and Brier scores. Additional metrics: F1 score, accuracy, precision, sensitivity, specificity, Youden index, PPV, NPR, PLR, NLR. Resulting CPRs: Discrimination assessed using AUC and calibration curves. Calibration assessed using calibration curves, slopes, and Brier scores. Clinical utility assessed via DCA relative to default strategies as well as CHA_2_DS_2_-VASc. Test tradeoff analysis will be used to balance ease-of-use with clinical utility.	Primary: LR—680 patients deemed necessary, see Appendix S5.3 in Supplementary Materials file S3. XGBoost—learning curve analysis and KL divergence will afford post hoc insight on suitability of sample size. 75% of AF dataset will be used, comprising 2072 AFAIS patients. Remaining 25% (691 patients) will be withheld as test set. Secondary: Entire AF dataset will be used, comprising 2763 AFAIS patients. Exploratory: Entire non-AF dataset will be used as supplementary test set, comprising 7809 AIS patients.	Models will be instantiated (LR with L2 regularisation and XGBoost with default hyperparameters) on AF dataset, randomly split into training (***T***, 75%) and test sets (***t***, 25%), preserving distribution of outcomes. Nested cross-validation (5 × 2) will be employed for training and hyperparameter tuning. After hyperparameters are optimised, final models will be retrained using the entire training set. The test set ***t*** will then be used for evaluation of final LR and XGBoost models, focusing on discrimination and calibration. Feature importance will be reported via coefficients and odds ratios (ORs) for LR and feature gain for XGBoost. To derive CPRs from these models, SHAP will quantify both main effects and interaction effects of predictor variables. Main effects, represented by mean SHAP values, will be used to rank and assign scores to each predictor, enabling the creation of interpretable and clinically applicable CPRs. Interaction effects, captured through SHAP interaction values, will further refine our CPRs by identifying significant synergistic or redundant relationships between predictors. These interactions will be incorporated into so-called ‘augmented CPRs’ in the form of accompanying rules. Both non-augmented and augmented CPRs will be evaluated on the test set ***t*** in terms of discrimination, calibration, and clinical utility. Clinical utility will be measured using NB via DCA, plotting NB against risk thresholds within the 0.01–0.20 range. The CPRs will be compared on the basis of clinical utility to one another, CHA_2_DS_2_-VASc, and default strategies (‘treat all’ and ‘treat none’). Test tradeoff analysis will evaluate whether any incremental benefit in clinical utility observed with augmented CPRs justifies the added complexity of incorporating accompanying rules. Secondary: CPRs (and not models) will be evaluated on the entire AF dataset for each secondary outcome via discrimination, calibration, and clinical utility. Exploratory: CPRs (and not models) will be evaluated on the entire non-AF cohort to assess generalisability and compare their clinical utility when applied to an unseen yet closely related patient population.	Discrimination will be classified as follows [101]: AUC of 0.81–0.90 = good, 0.71–0.80 = fair, 0.61–0.70 = modest, and 0.51–0.60 = poor. Miscalibration is detrimental to medical decision making and poor calibration has been coined the Achilles heel for CPR applicability [102]. As such, we consider at least as important as discrimination and give precedence to clinical utility, which provides a more comprehensive evaluation by integrating both discrimination and calibration when interpreting the performance of our CPRs. CPRs will be considered clinically useful at a given risk threshold only if their NBs exceed those of both default strategies. Of those deemed useful, we will rank the CPRs (including CHA_2_DS_2_-VASc) based on NB across the 0.01–0.20 risk thresholds. Test tradeoff (∆*N**B*) will be interpreted only insofar as spotlighting those CPRs which would be more conveniently deployable without sacrificing significant clinical utility.

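### CPR points are ranked on the signed mean SHAP value, which is zero or split noise under a same-population background, so the weights do not reflect the features' effects

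*Protocol article*

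**What the plan says.** In the Protocol article, CPR Development (under 2.12.6) takes the mean SHAP value, expressly not the mean absolute one: "SHAP values will be used in order to preserve information on the directionality of feature importance". Eight features are ranked. "The 25th, 50th, and 75th percentiles of the eight mean SHAP values will be computed", and then "Features belonging to the lower, middle, and upper tiers will be assigned one, two, and three points, respectively". Tables 3 and 4 repeat the rule: "Main effects, represented by mean SHAP values, will be used to rank and assign scores to each predictor".

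Two provisions could act as safeguards.
- **Zero points.** The rule opens with "In the rather unlikely event that one or more features will have negative mean SHAP values" and adds a second condition that must hold as well: "local SHAP value distributions that are consistently left of zero on the beeswarm plots, zero points will be assigned".
- **Skewed or concentrated means.** In that case "we will tailor tier boundaries using quantile-based binning".

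Elsewhere the article measures importance differently. Model Interpretation treats the mean absolute SHAP value as the indicator of global importance, and Global Interpretation says "we will calculate mean absolute SHAP values". The next part of CPR Development selects interaction pairs on the signed mean SHAP interaction value. The article names neither the SHAP variant nor the background set. It refers to a worked example in Appendix S6, which is not shown.

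**The concern.** A point in a clinical prediction rule should represent how much the predicted risk changes when a patient has the feature. The signed mean SHAP value averages patients with the feature (contribution on one side of zero) and patients without it (contribution on the other side). If the background comes from the same population, the two parts cancel. The statistic that orders the features then carries almost no information about their effects, and the percentile cuts turn that order into points.

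The points define the updated CPRs, and it is the CPRs, not the models, that are ranked on net benefit against CHA2DS2-VASc. The primary question in Table 3, whether the main effects differ after stroke, also cannot be answered by weights that do not track main effects.

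**Working it through.** The plan gives no figure for this step. Its related counts reproduce: 8 × 7 / 2 = 28 feature pairs, and 2763 × 0.75 and × 0.25 give 2072 and 691.

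**1. LR algebra (no assumed effects).** For binary feature i with coefficient b_i, SHAP_i = b_i (x_i − background prevalence). Averaged over the evaluation set:

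signed mean = b_i × (evaluation prevalence − background prevalence).

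If the two sets coincide, this is exactly 0. If the background is the training set T and evaluation is on the test set t, the difference is split noise with SD = sqrt[p(1−p)(1/691 + 1/2072)]. At p = 0.25 this is 0.0190. The expected absolute difference is 0.798 × 0.0190 = 0.0152, and the mean absolute deviation is 2p(1−p) = 0.375, so the signed mean is about 0.0152 / 0.375 = 4% of the mean absolute SHAP value. For p from 0.15 to 0.70 the ratio is 3.5% to 4.9%. The sign is a coin toss. Because the noise is multiplied by b_i, strong features swing to either end of the ranking while weak ones stay in the middle.

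**2. Any model, interventional SHAP.** The SHAP value of patient x against reference r is minus that of r against x. Averaging x and r over the same set therefore gives 0 for every feature. Numerical check with XGBoost, background equal to evaluation set: largest absolute mean 3e-16, while mean absolute SHAP values ran from 0.056 to 0.453.

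**3. Zero-point rule.** For a protective LR feature (b_i < 0), carriers have b_i(1 − p) < 0 and non-carriers have −b_i p > 0. The local values lie on both sides of zero, so the second condition fails.

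**4. Simulations.** Taken from the article: split sizes, recurrence rates of 5, 10 and 25% (within its 0.05–0.25 range) and XGBoost defaults; class weights were on in most runs. Assumed: eight binary features, prevalences 0.15–0.70 (0.22–0.70 in one of two simulations), log odds ratios 0.05–0.90 (0.05–0.70 in that one).

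| Quantity ranked | Mean rank correlation with true log ORs |
|---|---|
| LR, signed mean | 0.00 in one simulation; −0.06 to +0.11 in the other |
| LR, coefficient | 0.64 to 0.85; 0.73 to 0.89 |
| XGBoost, signed mean, interventional | −0.06 to +0.11; +0.10 to +0.18 in 15-run sensitivity checks |
| XGBoost, signed mean, path-dependent | −0.25 to −0.63 |
| XGBoost, present-minus-absent contrast | 0.62 to 0.87 |

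The SD of a rank correlation of eight unrelated items is 1/sqrt(7) = 0.38, so a mean of 15 has a standard error of about 0.10. The +0.10 to +0.18 values are compatible with chance.

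- About 4 of 8 signed means were negative for LR, and about 7 to 8 of 8 for XGBoost with path-dependent TreeSHAP.
- In one simulated cohort with only the split seed changed (LR), the strongest feature (log OR 0.90) got 1, 2 or 3 points in 36, 33 and 30% of splits; ranked by coefficient it got 3 points in 100%. The weakest (log OR 0.05) got 2 points in 84%.
- A protective feature (log OR −0.5) met the zero-point rule in 0 of 100 runs and averaged 2.1 points.
- AUC of the resulting score: 0.585–0.598 against 0.607–0.618 when ranked by coefficient (LR, one simulation). In the other, at 10% recurrence, 0.62 (LR) and 0.60 (XGBoost, path-dependent) against about 0.65.

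**The case against.** Several points on the other side have force.

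- **Unseen material.** Appendix S6 could define a reference patient or average over carriers only. With an all-absent reference the LR mean is b_i × prevalence, which correlated about 0.6 to 0.7 with the true effects, so it is not arbitrary. It still confounds effect with frequency: a factor with prevalence 0.15 would need a log OR 0.70/0.15 = 4.7 times as large to tie with one of prevalence 0.70. The article names no such reference.
- **Negative means.** A reader might infer that the article calls a negative mean unlikely and is wrong about that. It does not: the event it calls unlikely is a negative mean together with local values all to the left of zero. That combination is indeed rare, which is why the rule offers no protection.
- **XGBoost.** A reader might infer that XGBoost points reverse the true order. The negative correlation is only a tendency and appears only under path-dependent TreeSHAP, where the means are also not quite zero (9 to 24% of mean absolute SHAP). The article does not fix the variant.
- **Consequence.** A reader might infer that this alone decides the primary hypothesis. That is not shown. At AUC 0.60 in 691 patients the Hanley–McNeil standard error is about 0.052, 0.038 and 0.026 at 5, 10 and 25% recurrence, so a loss of 0.02 to 0.05 is of similar size, although paired comparisons are tighter.
- **Visibility.** Coefficients, gain, mean absolute SHAP and SAGE are all reported, so a discordant ranking could be noticed. Nothing in the plan would then correct the points.

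**Conclusion.** The point holds. As written, the ranking statistic does not measure a feature's effect. For LR with a same-population background, and for any model under interventional SHAP, this follows from algebra and needs no assumed effects. The re-binning fallback uses the same signed means, the zero-point rule is practically never met, and the stated aim of keeping direction is not achieved because a protective feature still earns points.

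The sizes (rank correlations, point shares and an AUC loss of about 0.02 to 0.05) rest on assumed effects and prevalences. The loss in discrimination is modest, but the point weights become largely arbitrary. The MLP-based rules and the interaction ranking use the same signed mean and were not simulated. Appendix S6 might define the mean differently; the article's text and tables would still need correcting.

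**What to change.** 1. In CPR Development and in Tables 3 and 4, rank and tier on the present-minus-absent contrast: mean SHAP among patients with the feature minus mean SHAP among those without it, computed in T on the log-odds scale. For LR this is b_i(1 − p) − b_i(0 − p) = b_i, the coefficient itself, so direction is kept.
2. Give zero points when the contrast is negative, in place of the present two-part condition.
3. Name the SHAP variant and the background set.
4. Replace the signed-mean ranking of interaction pairs with an analogous contrast, for example the double difference of the pair's SHAP interaction value across the four presence/absence groups.
5. Bring Appendix S6 into line if it follows the present text.

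The cost is wording in one section and two tables plus a few lines of code. No extra data are needed.

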### 2.4. Predictor Variables

The predictor variable in the validation analyses is CHA_2_DS_2_-VASc score, computed on the basis of its constituent features. It is computed as follows: 1 point for each of CHF, hypertension, DM, vascular disease (MI, CAD, or peripheral artery disease), age 65–74 years, and sex category (female), and 2 points for each of age ≥ 75 years and antecedents of AIS or TIA [24]. All features were measured at baseline, and, with the exception of age, all were binary encoded. As one of the more subjective items considered by CHA_2_DS_2_-VASc, peripheral artery disease was seldom recorded by contributing trials. Hence, MI and CAD will underlie the vascular disease feature.

The predictor variables in the updating analyses are the constituent features of CHA_2_DS_2_-VASc—omitting S_2_, which provides no discriminatory information in a cohort where all patients inherently have the same value (i.e., 2)—and previous stroke. Crucially, since secondary prevention is, by definition, aimed at patients having sustained an AIS, previous stroke is defined herein as any episode of AIS *prior* to the one that prompted recruitment. Besides preserving the familiar 7-feature structure of CHA_2_DS_2_-VASc, incorporating this variable in the updated CPR is very apropos in the modern-day context of effective treatment and demographic ageing which signify that many patients survive one or more strokes.

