### 2.12. Statistical Analysis

#### 2.12.1. Overview

We will validate the predictive performance of CHA_2_DS_2_-VASc for 90-day recurrence and secondary outcomes in the AF patient cohort by examining discrimination (AUC), calibration (calibration curves and Brier scores), and clinical utility (decision curve analysis). For CPR updating, we will use logistic regression (LR), extreme gradient boosting (XGBoost), and multilayer perceptron (MLP) models, with training and tuning performed through 5 × 2 nested cross-validation. The MLP model will employ transfer learning to incorporate information from the non-AF cohort. Model performance will be assessed on a hold-out test set using AUC, calibration curves, F1 score, and accuracy. We will utilise Shapley additive explanations (SHAP) for model interpretation and to construct two CPRs per model: one based on SHAP main effects and another incorporating both SHAP main and interaction effects. These CPRs will be evaluated against each other, CHA_2_DS_2_-VASc, and default strategies, with test tradeoff analysis to balance ease-of-use with clinical utility.

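### The main-effects logistic regression cannot supply the interaction evidence needed for its augmented CPR

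*Protocol article*

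**What the plan says.** Section 2.4 defines the inputs: "The predictor variables in the updating analyses are the constituent features of CHA_2_DS_2_-VASc", without the index-stroke item and with earlier stroke added. CPR Development counts them: "we have eight predictor variables corresponding to the features of CHA_2_DS_2_-VASc, namely five comorbid items, sex, and *two* age categories". The Model Building section gives the LR an L2 penalty and default settings on these inputs. No product terms are listed anywhere in the article. The Primary Analysis section presents LR as the linear baseline and brings in XGBoost to go beyond that restriction.

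The Overview nevertheless plans to "construct two CPRs per model: one based on SHAP main effects and another incorporating both SHAP main and interaction effects". CPR Development repeats this for every model: "Each of the CPRs will subsequently be augmented by integrating interaction effects", and "The decile rank of each of the twenty-eight mean SHAP interaction values from each model will be calculated". Pairs whose mean interaction value is above the 90th percentile are selected. Pairs with established synergy may enter if they fall somewhat short of it. Retained pairs and added points are each capped at three. The signed mean is used, not the mean of absolute values. The article does not say whether SHAP values are on the log-odds or the probability scale.

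**The concern.** The plan asks a model without interactions to report which interactions matter. LR is one of the two primary models, and whether interactions improve prediction is part of the primary question in Table 3. Its augmented CPR enters the net-benefit ranking. If it reaches the top three, it is compared with a non-augmented CPR by test tradeoff.

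Three things could go wrong:
- If the step is empty, two identical LR rules are ranked as if they were different.
- If rounding error or link curvature fills it, bonus points are reported as synergies that the model did not find.
- If domain knowledge fills it, the points rest on prior opinion but carry the label of a model-derived rule.

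**Working it through.** **Inputs from the article.** Eight features; main effects only in LR; selection strictly above the 90th percentile of the signed means; cap of three pairs; class weighting planned for LR (section 2.8); test set of 691 patients.

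**The plan's own count.** 8 × 7 / 2 = 28 pairs. This agrees with "We speak of twenty-eight mean SHAP interaction values because there are eight features". With 28 distinct values, the usual linear quantile leaves 3 strictly above the 90th percentile; some other definitions leave 2.

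**Log-odds scale.** The LR is f(x) = a + Σ b_k x_k, whatever the ridge penalty. For interventional SHAP, the value of a set S of known features is

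v(S) = a + Σ_{k in S} b_k x_k + Σ_{k not in S} b_k m_k, where m_k is the background mean of feature k.

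The interaction value for a pair (i, j) is a weighted sum, over all sets S without i and j, of

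v(S+i+j) − v(S+i) − v(S+j) + v(S).

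Substituting gives [b_i(x_i − m_i) + b_j(x_j − m_j)] − b_i(x_i − m_i) − b_j(x_j − m_j) + 0 = 0 for every S. All 28 values are therefore zero, for every patient and on average. The 90th percentile of 28 zeros is 0, and the number strictly above it is 0.

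**Numerical check.** Exact Shapley interaction values were computed over all 2^8 = 256 feature sets for a main-effects LR. The 691 rows match the planned test set. The coefficients, feature prevalences and intercepts are assumptions, because the article gives none, and the background was the same 691 rows. Class weighting was represented by an intercept shift from −3.5 to −1.0.

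| Scale | Mean predicted risk | Largest absolute mean interaction | Largest mean absolute main SHAP | Pairs strictly above the 90th percentile |
|---|---|---|---|---|
| Log-odds | not applicable | 2.5e-16 (rounding) | 0.25 | CHF–DM, CHF–sex, hypertension–DM, all from rounding |
| Probability, unweighted | 0.077 | 0.0018 | 0.019 | CHF–prior stroke, DM–prior stroke, prior stroke–age ≥75 |
| Probability, class-weighted | 0.481 | 0.00023 | 0.060 | hypertension–vascular, hypertension–prior stroke, vascular–age ≥75 |

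Run literally in floating point, the log-odds version still returns three pairs, chosen by rounding error. On the probability scale the selected means were about 0.00046 to 0.00054 unweighted and 0.00002 to 0.00003 weighted. No pair is common to the two lists, although the coefficients are identical and contain no interaction. Only the intercept moved.

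**The age pair.** The eight features include ages 65–74 and ≥75 as separate indicators. No patient can have both, so a bonus point for that pair can never be awarded. Usable pairs: 28 − 1 = 27.

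**Size.** Three models × two CPRs = six new CPRs, of which one is affected.

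**The case against.** The strongest reply is that the written rule gives a determinate and harmless answer. With 28 exact zeros nothing lies above the threshold, the augmented LR rule equals the plain one, their net benefits are identical, and the planned dot plot would show 28 values at zero. Domain-knowledge pairs can still enter, so the rule need not be empty. The worked example in Appendix S6 is not shown and may settle the scale and the empty case. Giving LR product terms would also depart from the article's wish to report feature importance in the same way across models.

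Much of this stands, and it limits the severity. It does not remove the defect, because no choice of scale or handling of ties makes an additive LR yield evidence of interaction. A duplicate rule would still be ranked as a separate CPR, and pairs added from domain knowledge would not come from the LR.

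Three stronger readings are tempting, and the article does not support them:
- **That the tie rule lets every pair in.** "Ties at quantile cut-points will be resolved conservatively by assigning them to the higher category" belongs to the paragraph on main-effect tiers. The interaction rule requires a value above the threshold, and the cap of three would stop 28 pairs entering in any case.
- **That any of the C(28,3) = 3,276 sets of three pairs satisfies the rule.** With exact zeros, none does. That count arises only if the tier rule is carried over to interactions.
- **That curvature on the probability scale counts the main effects twice.** The plan uses signed means. In a separate check with assumed inputs, their rank correlations with the product of the main effects were 0.05, −0.02, −0.27 and −0.59. Only mean absolute values tracked that product (0.93 to 0.97), and the plan does not use those for selection.

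**Conclusion.** The point holds in this form: the LR as specified cannot provide the interaction evidence that the Overview and CPR Development require from each model. On the log-odds scale the data-driven step is empty. On the probability scale it returns pairs that reflect the logistic link and the class weighting, not synergy.

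The zero result assumes interventional SHAP and no product terms, as the article describes the model. It would be wrong to infer that all 28 values are zero on every scale, or that the LR-augmented CPR must lack any content. What it lacks is content derived from the LR. The probability-scale figures rest on assumed coefficients and prevalences; they show that the selection can change, not which pairs VISTA would give.

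Severity is moderate. One of six new CPRs is affected. The validation of CHA2DS2-VASc, the LR main-effects CPR, and the XGBoost and MLP CPRs are not affected by the LR's lack of interaction terms.

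**What to change.** Choose one option before the data are analysed:

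1. **Drop the LR-augmented CPR** and state that five new CPRs will be evaluated. This costs wording only.
2. **Fit a second ridge LR in the training set T** with the interactions the article already names, and derive the LR bonus points from that model. CHF × age adds 2 terms, hypertension × age adds 2 and hypertension × DM adds 1, so five parameters are added. The cost is one more penalised fit and a small loss of parsimony. The original LR remains the source of the main-effects CPR.

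Under either option:
- State the scale of the SHAP values.
- State that no bonus point is added when no pair has a positive value above the threshold, and that values within rounding error count as zero.
- Label any pair admitted on domain knowledge as such, not as derived from the model.
- Remove the pair formed by the two age bands and take the percentile over 27 pairs. The linear quantile then sits at position 0.9 × 26 = 23.4, counting from zero, so three distinct values still lie above it and the cap need not change.
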